## Abstract

**Background:**

This paper presents a protocol for a randomised controlled trial of the Cardiac-Diabetes Transcare program which is a transitional care, multi-modal self-management program for patients with acute coronary syndrome comorbid with type 2 diabetes. Prior research has indicated people hospitalised with dual cardiac and diabetes diagnoses are at an elevated risk of hospital readmissions, morbidity and mortality. The primary aim of this study is to evaluate the effectiveness (and cost-effectiveness) of a Cardiac-Diabetes Transcare intervention program on 6-month readmission rate in comparison to usual care.

**Methods/Design:**

A two-armed, randomised controlled trial with blinded outcome assessment will be conducted to evaluate the comparative effectiveness of two modes of care, including a Usual Care Group and a Cardiac-Diabetes Transcare Intervention (in addition to usual care) Group. The primary outcome is 6-month readmission rate, although a range of secondary outcomes will be collected (including self-efficacy) at baseline, 1, 3 and 6 month reassessments. The intervention group will receive in-hospital education tailored for people recovering from an acute coronary syndrome-related hospital admission who have comorbid diabetes, and they will also receive home visits and telephone follow-up by a trained Research Nurse to reinforce and facilitate disease-management-related behaviour change. Both groups will receive usual care interventions offered or referred from participating hospital facilities. A sample size of 432 participants from participating hospitals in the Australian states of Queensland and Victoria will be recruited for 90% power based on the most conservative scenarios modelled for sample size estimates.

**Discussion:**

The study outlined in this protocol will provide valuable insight into the effectiveness of a transitional care intervention targeted for people admitted to hospital with cardiac-related presentations commencing in the inpatient hospital setting and transition to the home environment. The purpose of theory-based intervention comprising face-to-face sessions and telephone follow up for patients with acute coronary syndrome and type 2 diabetes is to increase self-efficacy to enhance self-management behaviours and thus improve health outcomes and reduce hospital readmissions.

**Trial registration:**

This study has been registered with the Australian New Zealand Clinical Trials Registry dated 16/12/2014: ACTRN12614001317684.

## Background

Cardiovascular disease and diabetes mellitus are contributing to a dual chronic disease epidemic. The Organisation for Economic Co-operation and Development (OECD) reported data compiled from its member’s countries in 2011, identifying that these diseases caused nearly one-third of all recorded deaths [1]. Estimating numbers of patients with both conditions is difficult as data have been primarily collected with single-disease specificity, despite acknowledgement of increasing multi-morbidity [2]. In Australia, where the present study is being conducted, it is difficult to illustrate a complete picture of the proportion of cases of cardiovascular related disease and diabetes, in particular type 2 diabetes mellitus, as there are no national registries of these diseases [3].

Historically, the patient self-management programs that have shown to improve clinical outcomes have focussed on a specific disease or clinical presentation. However, patients with both cardiac conditions and diabetes have higher rates of re-hospitalisation than those with only one disease [4]. A previous study by investigators of this trial identified that patients with both acute coronary syndrome (ACS) and type 2 diabetes were three-fold more likely to be readmitted to an acute hospital within 28 days of discharge, compared to patients with only ACS [4]. Higher readmission rates translate to greater impact physically, emotionally and financially for patients and health services [5].

Inpatient hospital education programs can influence a patient’s management of their chronic disease, yet there is inconclusive evidence on adherence to treatment recommendations for patients with multiple conditions [6]. Qualitative evidence from patients’ perspectives has indicated that disease management programs that only focus on one of an individual’s multiple chronic conditions can create confusion and uncertainty regarding which condition should take priority for treatment [7]. Discharge planning models of care have been identified for patients with singular chronic diseases, and for older patients identified as having risk factors for readmission [8]. A Cochrane Review published in 2013, reported that when discharge planning is tailored to individual needs it is more likely to lead to a reduction in readmission [9]. The present study includes an intervention that can be tailored to the individual needs of patients with both cardiac disease and diabetes with the intention of increasing patients’ self-efficacy in managing both of these conditions.

Programs incorporating strategies promoting self-efficacy have demonstrated potential to translate into behaviour change [10]. The features of the cardiac-diabetes self-management program (CDSMP) to be evaluated in the present study have been discussed in detail previously [11–15]. In summary, the CDSMP has been developed for patients with dual cardiac and diabetes diagnoses and strategies included in the program have their foundation in Bandura’s theory of self-efficacy [16, 17]. Literature examining different program delivery modalities has indicated that a combination of an in-hospital multi-media based education, followed by an early in-home visit and telephone call follow-up can be a relatively inexpensive, interactive and effective approach for reducing unplanned hospital re-admissions [18]. However, this approach has not been trialled specifically among a population of cardiac patients with type 2 diabetes, which is the target clinical group for the Cardiac-Diabetes Transcare intervention to be trialled in this investigation.

### Aims

The aims of the proposed study are to evaluate the effect of the Cardiac-Diabetes Transcare Program on the primary outcome of 6-month readmission rates, as well as secondary outcomes of health status, health-related quality of life, and self-efficacy that will be recorded at baseline, 1, 3, and 6 months. A further aim is to evaluate the cost-effectiveness of this intervention from the perspective of the healthcare system.

## Methods

### Design

A two armed, randomised controlled trial with blinded outcome assessment will be conducted with a 6 month follow-up (Fig. 1). This trial will evaluate the comparative effectiveness of Usual Care (Group 1) and the Cardiac-Diabetes Transcare Program (Intervention) which will provide education, in-home visits and telephone follow-up by a Research Nurse (ResN) in addition to their usual care (Group 2).

**Fig. 1 Fig1:**
[figure not shown]
Study design and procedure overview

### Sample size considerations

A target sample of 432 patients (with an anticipated attrition rate of 20% over the 6 month follow-up period) will be recruited from participating hospital facilities in Australia. The participating hospitals include the Royal Brisbane and Women’s Hospital (929-bed tertiary referral public hospital, located in Brisbane, Queensland, Australia), and the St Vincent’s Hospital, Melbourne (504-bed tertiary referral metropolitan hospital, located in Melbourne, Australia).

Completed data on 173 patients per group will enable over 90% power to detect 17.5% difference between groups in 6-month readmission rate (30% versus 47.5%) with alpha = 0.05. The assumptions for this sample size calculation were based on a more conservative anticipated effect than the large effect observed in a subgroup of patients (*n* = 49) with comorbid cardiac condition and diabetes from a randomised trial previously conducted by investigators of the present trial [8]. The previous study similarly included an intervention comprising a home visit and 6-month follow up, but was not tailored for patients with dual ACS and type 2 diabetes and instead targeted older adults who had been hospitalised. The sub-group analysis indicated a large effect of the intervention resulting in a 31.5% (intervention 25.0% versus usual care 56.5%) between group differences in raw 6-month readmission rates.

However, due to potential differences in sample characteristics between the prior trial sub-group and the target sample of the present study that may be associated with readmission rates, an interim analysis of hospital re-presentation event rate will be undertaken. This analysis will examine the 3-month readmission rate in the present study (both groups combined) to see whether it is higher or lower than rates used in the sample size calculation. This will be conducted using the first (approximately) 10% of the target sample to reach the 3-month re-assessment point, by a statistician not involved in the day-to-day operations of the trial. The statistician will be provided with a dataset from each trial site that does not include a variable for group allocation and no attempt to compare event rates between groups during the interim analysis will occur. Rather the sole purpose of the event rate interim analysis is to verify or refute whether the difference in readmission rates used in the initial sample estimate is plausible. If the event rate is substantially discordant with the sample size estimate the investigation team will decide whether an amendment to the trial protocol is warranted, and appropriate approvals (e.g., from ethical review boards) will be sought.

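### The blinded interim check sets a 3-month readmission rate against 6-month planning rates, and its stated purpose, to verify or refute the planned difference, cannot be met with pooled data

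*Protocol article*

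**What the plan says.** All of this is in the protocol article, Methods, Sample size considerations.

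- The sample size is set to detect a "17.5% difference between groups in 6-month readmission rate (30% versus 47.5"%), with 173 completers per group. The prior-trial subgroup behind it (25.0% versus 56.5%) is also reported at 6 months. No 3-month rate appears.
- The interim analysis is to "examine the 3-month readmission rate in the present study (both groups combined) to see whether it is higher or lower than rates used" for planning.
- On its size: "This will be conducted using the first (approximately) 10% of the target sample to reach the 3-month re-assessment point".
- The dataset "does not include a variable for group allocation and no attempt to compare event rates between groups during the interim analysis will occur".
- Its sole purpose is nevertheless to "verify or refute whether the difference in readmission rates used in the initial sample estimate is plausible".
- On the consequence: "If the event rate is substantially discordant with the sample size estimate the investigation team will decide whether an amendment to the trial protocol is" justified; ethics approvals would follow.

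**The concern.** There are two faults, and both lie in what the article states rather than in what it omits.

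First, the horizons differ. The cumulative proportion readmitted by 3 months cannot exceed that by 6 months, and the two are equal only if nobody has a first readmission after month 3. Set against 6-month planning rates, the 3-month rate is therefore expected to look low with every planning assumption true. The team could then consider an amendment for a trial that is on course.

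Second, the purpose does not fit the data. A dataset with no allocation variable, from which groups will not be compared, is said to verify or refute a between-group difference. A pooled rate close to the planned one could be read as support for the 17.5-point assumption when it supports only the overall event rate.

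**Working it through.** **Inputs.** From Sample size considerations: 30% and 47.5% at 6 months, 173 completers per group, alpha 0.05 (two-sided assumed), target 432, interim at about 10%, prior subgroup 25.0% versus 56.5%. From the randomisation section: 1:1 allocation.

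**The plan's own figure.** The usual two-proportion formula for 30% versus 47.5% at 90% power gives 161 per group, or 173 with the continuity correction, which matches. Without the correction, 173 per group has 92% power. Also 432 × 0.8 / 2 = 172.8. The sample size reproduces, so the fault is confined to the interim check.

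**Comparator and interim size.** Pooled 6-month rate = (0.30 + 0.475)/2 = 0.3875. Interim n = 0.10 × 432 ≈ 43.

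**Expected 3-month rate (assumed; none is given).** With a constant hazard in each arm, p3 = 1 − √(1 − p6):
- 1 − √0.70 = 0.163
- 1 − √0.525 = 0.275
- mean 0.219

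If readmissions come earlier, the 3-month rate is higher. The upper end taken here is 31%, which is 80% of 38.75% (0.80 × 0.3875 = 0.31).

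**Chance of a discordant result when the plan is exactly right (n = 43, binomial).** The trigger is also assumed, so two are shown.
- Trigger A: 95% interval wholly below 38.75%. This needs 10 or fewer events (Wilson and exact intervals agree).
- Trigger B: 95% Wilson interval wholly below the lower planning rate, 30%. This needs 7 or fewer events.

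| True pooled rate | A: P(X ≤ 10) | B: P(X ≤ 7) |
|---|---|---|
| 21.9% (constant hazard) | 66% | 24% |
| 25% | 48% | 12% |
| 28% | 31% | 6% |
| 31% | 18% | 2% |
| 38.75% (6-month data, like for like) | 2.4% | 0.1% |

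**Precision.** The 95% half-width at 38.75% is 1.96 × √(0.3875 × 0.6125/43) = 0.146, or 14.6 points, close to the whole planned difference of 17.5 points.

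**What a pooled rate says about the difference.** These pairs all pool to 38.75%; the power is at 173 per group:

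| Usual care v intervention | Difference (points) | Power |
|---|---|---|
| 47.5 v 30 | 17.5 | 92% |
| 45 v 32.5 | 12.5 | 67% |
| 42 v 35.5 | 6.5 | 24% |
| 38.75 v 38.75 | 0 | no effect to detect |

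The prior subgroup's 31.5-point difference pools to (25.0 + 56.5)/2 = 40.75%, only 2 points from 38.75%. With a half-width near 15 points, the check cannot separate differences of 31.5, 17.5 and 0.

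A pooled rate p does bound the difference. At 1:1 the difference cannot exceed 2p when p is below 50%, so 17.5 points becomes impossible only when the pooled 6-month rate is below 17.5/2 = 8.75% (by symmetry, above 91.25%).

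**The case against.** **The trigger is not in the protocol.** This stands. The article names neither 38.75% nor a confidence-interval rule; it refers to rates in the plural and leaves discordance to judgement. The result depends on the trigger as much as on the assumed 3-month rate, which is why both are varied. A reader might infer that the check will trigger an amendment, or does so with 66% probability. The documents do not support that: 66% needs both a constant hazard and trigger A, and an amendment needs a team decision and approvals. Nor is a lower observed rate certain: at a true 31%, 17 or more events in 43 (above 38.75%) occur about 15% of the time.

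**The procedure is really an event-rate check.** Largely fair. The passage is introduced as "an interim analysis of hospital re-presentation event rate will be undertaken" and acts on the event rate. Such a blinded check is legitimate and costs no alpha. But the sentence on sole purpose says something else, and the comparator is wrong for an event-rate check too.

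**Pooled data are not wholly uninformative.** Correct. A reader might say they carry no information on the difference. An extreme pooled rate could make the planned pair implausible; one anywhere near 38.75% cannot.

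**Other stronger readings.** The article uses both re-presentation and readmission, but the next sentence specifies readmission, so the event is not seriously in doubt. Nor is this shown to be the only safeguard: the planned difference is already smaller than the one observed earlier, and the limitations section mentions power calculations for smaller samples. A numeric threshold may sit in the full protocol, so its absence is not counted here. An early look at 10% is a defensible trade-off for catching gross discordance.

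**Conclusion.** The point holds in two parts. The interim comparison mixes a 3-month observation with 6-month planning rates and so leans towards a false signal of too few events: 66% down to 18% under trigger A and about 24% down to 2% under trigger B, for assumed 3-month rates of 21.9% to 31%. On a matched horizon, trigger A gives about 2%. Separately, the stated purpose cannot be met with blinded pooled data unless the pooled rate is very low or very high. The first part's direction follows from the text; its size rests on a 3-month rate and a trigger that the documents do not give. Severity is should-fix: the look is blinded, nothing changes automatically, and neither the primary analysis nor the reproduced sample size is affected.

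**What to change.** 1. Restate the purpose as a blinded check of the overall event rate, and delete the claim that it verifies or refutes the planned difference.
2. Compare on one horizon. Either derive an expected pooled 3-month rate from the planning rates and record it before the look, or set the pooled 6-month proportion against 38.75%.
3. State that with about 43 patients (half-width about 15 points at 38.75%) the check can reveal only gross discordance.

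The cost of items 1 and 3 is wording. For item 2, a 3-month target needs a stated assumption about when readmissions occur; a 6-month look needs none but comes later and leaves less time to act. No accrual rate is given, so that delay cannot be put in calendar terms. A larger interim sample is optional: at 25% of the target (108 patients) the half-width is 1.96 × √(0.3875 × 0.6125/108) = 9.2 points, but the look is later still. None of this needs extra trial patients or spends alpha, provided that the look stays blinded.

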### Recruitment

Patients admitted to study hospitals will only be approached for potential participation if they meet the following inclusion criteria: diagnosed with acute coronary syndrome (ACS) and type 2 diabetes. Acute coronary syndrome is defined as ST-segment elevation myocardial infarction (STEMI), non-STEMI, or unstable angina [19]. Participants will be excluded from participation in the study if they are critically ill, unconscious, on respiratory ventilation, and/or have a current significant cognitive impairment, determined by the treating specialist or his/her nominated physician. Patients eligible for participation will be provided with a participant information and consent form and will be required to provide written informed consent prior to their participation.

Prior to baseline data collection, eligible patients will be recruited by a research assistant (RA) during their hospital admission. The RA will be a hospital staff member and will obtain individual patient’s informed consent. Consenting participants will then be assigned a trial participant number which will be used during the randomisation process where they will be allocated to either the control or intervention group.

### Randomisation, concealment and group allocation

A computerised random number sequence generated by an independent statistician (not involved in the day-to-day trial) will be used to allocate each participant to the control or intervention group in a one-to-one ratio. Group allocation is concealed in opaque envelopes that stored in a lockable filing cabinet accessible to a randomisation gatekeeper (an administration officer not otherwise involved in the conduct of the trial). After a patient has been recruited, the member of the research team responsible for co-ordinating intervention allocation will telephone the randomisation gatekeeper to reveal the group to which that participant has been allocated. Group allocation will then only be known by the randomisation gatekeeper, the person responsible for the intervention allocation and those providing the intervention (ResN) at each participating site. Participants will not be directly told their group allocation (in terms of usual care or intervention). Control group participants will continue to receive the usual standard care while participants in the intervention group will receive usual care as well as the Cardiac-Diabetes Transcare Program.

### Intervention: cardiac-diabetes transcare program

#### While in hospital

After randomisation the ResN visits the participant in hospital and delivers 2 education sessions. These sessions focus on:assessing the patient’s knowledge of their conditions and their skill and confidence in their self-management;providing the patient with examples or models of someone with similar conditions, by showing them relevant segments or the entirety of the digital video of the Cardiac -Diabetes Self-Management Program, “Refocusing Your Life” [12]. The participant will then be given a copy of the digital video (e.g. a Digital Video Disc), a new blood glucose meter and lancing device as well as supplies and blood glucose recording sheets. Opportunities for questions and answers will also be provided during these sessions.

#### After discharge home

The ResN will conduct an in-home visit within the first week post hospital discharge. The visit will ensure participants: 1) have sufficient support and required information; 2) understand individual management goals; 3) are able to carry out self-management activities in the home environment; 4) understand their treatment regimens; and 5) are provided reinforcement and further necessary explanations of self-management.

Following the home-visit, the nurse will conduct weekly telephone follow-ups for 4 weeks, and monthly up to 6 months. The purpose of the individual telephone calls is to ensure participants continue to monitor and manage their conditions, to update their self-management goals according to individual recovery, as well as providing encouragement and feedback to the participant. For patients allocated to the control group, participants will receive usual standard care including routine rehabilitation advice and being referred to a local diabetes educator as the usual treating clinical team deem necessary.

#### Data collection

A RA blinded to group allocation will undertake all data collection. Baseline data will be collected by the RA at the patients’ earliest convenience (within 48 h of recruitment). Follow-up assessments (1, 3 and 6 months) will be conducted at a location convenient for the participant (e.g. at their home) and will be recorded by the RA.

#### Measures

Outcome measures will include: The primary outcome for effectiveness is readmission to hospital, as recorded in patients’ medical record, hospital administrative records, or patient report of readmission to a non-participating hospital (e.g. while travelling). Secondary outcomes include health status (e.g. blood pressure, blood glucose levels documented on the medical record), Assessment of Quality of Life (AQoL) [20] for health-related quality of life, Self-efficacy for Managing Chronic Disease 6-item Scale [21] for self-management, Medical Outcomes Study Social Support Survey [22] for psychosocial well-being, Patient self-report for Health Service Utilisation Questionnaire [23] as well as Medicare and Pharmaceutical Benefits Scheme claims information, and hospital administrative data for healthcare related resource usage to which healthcare costs will be attributed.

### Data analysis

Data analysis will be conducted using intention-to-treat principles. The following analyses will be undertaken:Baseline data for both the intervention and control groups will be examined to check for similarity of the groups. Variables with potential differences between groups at baseline will be controlled for during subsequent analyses.Comparisons between groups will be undertaken to examine the effect of being allocated to the intervention versus control group on the primary and secondary outcomes using generalised linear mixed modelling. These analyses will be adjusted for age and gender in addition to any variables with potential between group differences identified at baseline.Healthcare costs (healthcare system and intervention-related costs) over the 6-month follow-up will be summarised for control and intervention group participants.A trial based economic evaluation will also be conducted alongside the randomised controlled trial (RCT) to quantify the additional costs (or cost savings) per health benefit (Quality Adjusted Life Years (QALYs)) attributable to the intervention in comparison to usual care alone. This will be expressed in the form of an incremental cost effectiveness ratio. All costs will be measured in Australian dollars for the year of study completion. Bootstrap re-sampling of trial data will be used to construct 95% confidence ellipses and cost-effectiveness acceptability curves will be prepared. Sensitivity analyses will be conducted to examine the robustness of these estimates to change in cost, effect, time-horizon, and background context data.

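### Beyond age and gender, covariates are chosen by looking for baseline differences between arms, so the primary and secondary models are not fixed in advance and rest on chance imbalance rather than prognosis

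*Protocol article*

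**What the plan says.** All of this is in the protocol article, Methods, Data analysis. The first step is a comparison of the arms: "Baseline data for both the intervention and control groups will be examined to check for similarity of the groups". The consequence follows directly: "Variables with potential differences between groups at baseline will be controlled for during subsequent analyses". The rule is then built into the mixed models that estimate the treatment effect for every outcome, primary and secondary alike. The adjustment is worded as follows: "These analyses will be adjusted for age and gender in addition to any variables with potential between group differences identified at baseline".

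So two covariates are fixed and every other one depends on what the baseline comparison shows. The section does not say what counts as a *potential* difference, which variables are candidates, or who decides. Nothing elsewhere in the article limits or replaces the rule.

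**The concern.** Allocation is by a computerised random sequence in a 1:1 ratio (Randomisation, concealment and group allocation). Differences that predate allocation are therefore chance, and their size says nothing about whether a variable predicts the outcome. A rule triggered by imbalance can bring in a variable of no prognostic value and leave out a useful one that happens to look balanced.

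Two things are at stake. First, the primary model is not known until allocation-labelled data have been read, and two analysts could read the same baseline table differently. Second, a test that adjusts only when imbalance is seen does not hold its nominal level when the covariates are prognostic. In the samples that look balanced, the unadjusted standard error is too wide for the variation that remains, so the test is conservative and gives up power.

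This is not a detail left to an unseen analysis plan. The article states the selection rule, and a later plan could repair it only by contradicting it.

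**Working it through.** **1. The plan's own figures.** Inputs from Sample size considerations: 173 completers per arm, of which the section says that they "will enable over 90% power to detect 17.5% difference between groups in 6-month readmission rate (30% versus 47.5%) with alpha = 0.05". Sidedness is not stated; two-sided is assumed. The pooled proportion is (0.475 + 0.30)/2 = 0.3875.
- SE under the null = √(2 × 0.3875 × 0.6125/173) = 0.0524.
- SE under the alternative = √((0.475 × 0.525 + 0.30 × 0.70)/173) = 0.0515.
- Power = Φ((0.175 − 1.96 × 0.0524)/0.0515) = Φ(1.40) = 92.0%, or 90.2% with continuity correction.
- Completers: 432 × 0.8/2 = 172.8 per arm.

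The stated figures reproduce, so the sample size is not at fault here.

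**2. How often the model would change.** The number of candidates and the trigger are assumptions. With 10 independent baseline variables, the chance that at least one is flagged is:
- trigger p<0.05: 1 − 0.95^10 = 40%;
- trigger p<0.10: 1 − 0.90^10 = 65%;
- trigger p<0.20: 1 − 0.80^10 = 89%.

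A change from the age-and-gender model is therefore likely under many readings of the rule.

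**3. Continuous secondary outcome.** Assumed: one follow-up, 173 per arm, baseline-outcome correlation ρ of 0.5 or 0.7, effect 0.3 SD, and adjustment for baseline only if its imbalance has p<0.10. In large samples:
- Unadjusted: mean of the test statistic = 0.3 × √(173/2) = 2.79; power = Φ(2.79 − 1.96) = 80%.
- Always adjusted: the mean becomes 2.79/√(1 − ρ²). For ρ = 0.5 this is 3.22 and power is 90%; for ρ = 0.7 it is 3.91 and power is 97%.
- Imbalance rule under the null: baseline is flagged in 10% of samples and the adjusted test then rejects 5% of the time, contributing 0.10 × 0.05 = 0.5%. In the other 90% the unadjusted test is used, and numerical integration gives a contribution of 3.5% (ρ = 0.5) or 2.5% (ρ = 0.7). The totals are 4.0% and 3.0%.
- Imbalance rule under the alternative: the same integration gives power of 82% and 83%. Simulation with 10,000 replicates gave 81% and 83%.

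| ρ | Type I error, imbalance rule | Power, imbalance rule | Power, always adjusted |
|---|---|---|---|
| 0.5 | 4.0% | 81% | 90% |
| 0.7 | 3.0% | 83% | 97% |

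**4. Primary outcome.** Simulated with a logit link (not stated in the article), 173 per arm, age and gender always in the model, and ten candidates of which two are prognostic. There were 8,000 null runs (standard error about 0.0024) and 4,000 runs under the planned rates.
- Prognostic score SD 1.0 to 1.5 on the logit scale: type I error 0.036 to 0.045 under triggers from p<0.05 to p<0.20, against 0.048 to 0.049 with the prognostic covariates fixed in advance. Power is 92.9% to 94.3% under the rule, 96.3% to 97.7% with those covariates fixed, and 92.1% to 92.9% with age and gender only.
- Score SD 0.5: type I error 0.052 to 0.055 under the rule against 0.055 with fixed covariates, and power about 92% against 93%. The rules barely differ.

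**5. If the choice of model followed the results.** Taking the most favourable of the age-and-gender model and the three selected models gives type I error of about 0.06 for the primary outcome. Taking the better of two models for the continuous outcome at ρ = 0.5 gives 0.073. The article does not describe such a procedure; these figures only show what a fixed model rules out.

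**The case against.** The case on the other side is substantial.

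- **A reader might infer that readmission loses power and that the fix recovers it.** The documents do not support this. Age and gender are already fixed, so the fix adds only hospital, whose prognostic strength is not given. The higher power in step 4 comes from two assumed predictors that the article does not name. The age-and-gender model, which is the nearest to the fix, has slightly less power than the imbalance rule, and every scenario stays above the planned 90%. This objection stands in full.
- **A reader might infer that the rule inflates the error rate or lets the result be picked.** The article places the baseline check before the outcome models and selects on baseline data, not outcomes. Mechanical use is conservative; inflation requires choosing among models after seeing results. What remains is that the undefined trigger does not exclude that choice.
- **A reader might infer that baseline scores are dropped from secondary models whenever they look balanced.** The planned generalised linear mixed models could treat baseline as one of the repeated responses (it is recorded alongside months 1, 3 and 6), which would use it regardless of balance. The article does not say either way, so step 3 is an illustration and not a forecast.
- **Always adjusting for baseline is not safe as the trial now runs.** Baseline may be taken up to 48 hours after recruitment (Data collection). Allocation is revealed after recruitment, and the in-hospital education follows randomisation. A baseline score could then already carry an intervention effect. This stands and is made a condition of the fix.

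**Conclusion.** The point holds in a limited form. The rule that models be "adjusted for age and gender in addition to any variables with potential between group differences identified at baseline" leaves everything beyond age and gender undetermined until the arms have been compared, and selects on chance imbalance instead of prognosis. That is a poor rule for a confirmatory analysis, whatever its numerical cost.

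The size depends on inputs that the document does not give: predictor strength, number of candidates, trigger and model form. For a continuous outcome under the assumptions of step 3, type I error falls to about 4% or 3%, and power is about 9 points (90 − 81) or 14 points (97 − 83) below that of always adjusting. With weak predictors, or with baseline as a repeated response, the loss is smaller or absent. For readmission, mechanical use is mildly conservative with moderate to strong predictors and makes little difference with weak ones. What the fix brings to readmission is a model settled in advance, not extra power. Neither the sample size nor the validity of the trial is called into question. It should be fixed, but it is not a fatal flaw.

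**What to change.** Delete the imbalance rule from Data analysis and from any analysis plan that repeats it. Before allocation-labelled data are examined, state the covariates:

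- readmission: age, gender and hospital;
- each secondary outcome measured at baseline (AQoL including the utility used for QALYs, self-efficacy, social support): the same set plus that outcome's own baseline value, provided baseline is collected before allocation is revealed.

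Report baseline balance descriptively. Show any model that adds imbalanced variables only as a labelled sensitivity analysis.

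The cost is some rewording and one procedural step: completing the baseline assessment before the telephone call that reveals allocation. No extra participants are needed, and the baseline measures are already planned.
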